**Intestinal Barrier Function Changes in Response to Administration of Corticotropin Releasing Hormone and High Fat Diet**

**Background**

| The last decade has seen a number of studies supporting the theory of chronic intestinal barrier perturbation in the pathogenesis of IBD and many other human diseases.^1–4^ Stress – a state which evokes a ‘fight or flight’ or sympathetic response from the human organism - has been implicated in the propagation of inflammation in patients with inflammatory bowel disease (IBD). Indeed, the risk of relapse in both Crohns disease (CD) and Ulcerative colitis (UC) increases in the presence of both acute and chronic stress. ^5–7^ The mechanism proposed for this phenomenon includes the ability of stress to induce a breakdown in intestinal barrier function via mast cell- and corticotropin releasing hormone (CRH)-dependent pathways. ^8^ This intestinal barrier perturbation has been demonstrated experimentally in humans using stress paradigms which could be equated to the relatively mild stressful events experienced in every-day life, such as public speaking.^9–11^, although replicating this has practical difficulties in a research setting. Another established way to induce intestinal stress is through diet.  The autonomic nervous system (ANS) appears to be playing a crucial role in stress-induced changes in intestinal permeability. Multiple in vitro and in vivo murine model studies have confirmed that both acute and chronic stress (induced in a mouse by various stress paradigms such as restraint and water emersion) can promote increased intestinal permeability. The underlying mechanism seems to be via the disruption of tight junction proteins along the paracellular space of the intestinal epithelium.^15,16^ The disruption of tight junctions in these stress paradigm models are dependent on acetylcholine and CRH. ^11,17^ This effect on intestinal permeability appears to recover within 4 days in murine models.^18^ Similar changes have been described in human models of acute stress. Changes in intestinal permeability induced by acute stress can be mimicked by peripheral administration of CRH.^19^  Corticotropin releasing hormone (CRH) is naturally secreted from the healthy human hypothalamus during periods of stress. Intravenously administered CRH possesses the advantage of having a short half-life and is routinely clinically utilised in the diagnosis of Cushing’s syndrome.^12,13^ Recent evidence has shown that injecting CRH intravenously reliably and significantly increases intestinal permeability in healthy volunteers with no significant adverse effects.(12) The timeline of this increase, and its effect on the serum intestinal permeability measurements have not been established.  Food-induced stress has also shown to temporarily impair barrier function in healthy subjects with a standardised ‘high fat high carbohydrate’ meal. This challenge meal, comprising 50-60 g fat and 80 g carbohydrate, caused bacterial translocation indicated by increased sCD14 and LBP^14^, although it is not known if these changes are maintained beyond four hours. This standardised meal has been used in research setting in many studies and is accepted as gold standard. However, using food as a model to represent IBD has its limitations. Food is complex in its composition and has many confounding nutrient factors, background diet is rarely considered and may impact outcomes, blinding is difficult, recruitment of study participants will automatically exclude those with dietary restrictions or certain food dislikes and using food-induced stress is not appropriate for trials investigating dietary therapies. Furthermore, it is difficult to translate the findings into real world, which involves constant ingestion of food. We need a more reliable model of experimentally inducing intestinal barrier dysfunction in humans.  Several serological and urinary markers have been validated as useful tools in measuring intestinal  permeability changes in vivo. These include lipopolysaccharide-binding protein (LBP), soluble CD-14  (sCD14), syndecan-1 and intestinal-type fatty acid-binding protein (I-FABP) in the serum. Because  sCD-14 and LBP are part of the LPS inflammatory signalling pathway, their levels in serum are believed  to be objective markers for systemic immune activation and damage to gut epithelium.^14,20^.  I-FABP is an intracellular protein expressed in the epithelial cells of the mucosal layer of the small  and large intestine tissue and is prone to leakage into the blood stream from the enterocytes when  intestinal mucosal damage occurs.^21^ Syndecan-1 is a key component of the glycocalyx layer of the  intestinal endothelial surface.^21^ Syndecan-1 is crucial to the maintenance of the intestinal epithelial  barrier function^22^ and its release into the circulation indicates perturbation of the intestinal barrier.^23,24^  While I-FABP and syndecan-1 are preformed and would be rapidly released on intestinal injury in association with acute stress, such as a single meal (as above) or CRH administration, the validity of the serum/plasma markers, LPB and sCD14, requires critical examination. The response of these markers is dependent upon new protein synthesis in response to cytokine release (specifically IL-1, IL-6 and TNFα) related to increased LPS/endotoxin exposure following changes in barrier function. Since such production is transcriptionally regulated, there will be a delay in detecting a rise in the concentrations of LPB and sCD14. In rabbits stimulated with silver nitrate, transcription had a delay of up to 2 hours. Subsequent LBP levels in serum were elevated at 4 hours after the stimulus and were maximal at 24 hours.^25^ The studies examining LPB and sCD14 after a high fat meal had changes observed within the first 2 hours.^14^ This is not easy to reconcile with new induction of protein synthesis and might reflect washing out of hose proteins from the intestinal mucosa via increased lymphatic flow, as previously shown for hyaluronic acid.^26^ Whatever the case, the question of the time course of events requires clarification.  We aim to develop a model of intestinal permeability perturbation in healthy human volunteers with both CRH and a standardised high fat high carbohydrate meal. This will allow for future studies to experimentally test therapeutic efficacy of CRH on the intestinal barrier function.  **AIMS:**   1. To develop models of intestinal permeability perturbation in healthy human volunteers utilising 2 strategies  - Physiological stress induction by intravenous CRH injection - Clarification and further exploration of the stress effect of a standardised high-fat high-carbohydrate (HFHC) meal on intestinal barrier dysfunction. This data will be used in future studies to dissect out the particular dietary components within this meal which specifically induce permeability changes.  1. To characterise the models in terms of optimal timing of blood sampling circulating markers of intestinal barrier dysfunction   **HYPOTHESES:**   1. Both CRH and the high-fat high-carbohydrate meal will increase intestinal permeability over a normal saline injection as measured by serum markers of intestinal permeability (I-FABP, Syndecan-1, CD14 and LBP). 2. There are differences in optimal timing of the measurement of circulating markers.     **Project Design**  This will be a single centre, randomised, placebo-controlled cross-over study to investigate the effect of CRH and a HFHC meal on intestinal permeability. (See ***Figure 1***).  ***Figure 1***  ***[figure not shown]***  **Inclusion criteria:**   - Healthy males and females between the ages of 18 – 65 - Participants who are able to give informed consent - Volunteers should be able to attend Monash University, Alfred Campus on 7 occasions   **Exclusion Criteria**   - Inclusion criteria not met - Past medical history of diabetes (type 1 or 2) - Past medical history of inflammatory bowel disease, coeliac disease, a diagnosis of irritable bowel syndrome or significant gastrointestinal symptoms not otherwise medically diagnosed - Patients actively taking non-steroidal anti-inflammatory medications (NSAIDs) or corticosteroids - Probiotic or antibiotic intake over the past 2 months - Pregnant or breast feeding participants - Allergy or intolerance to the components of the proposed meals   **Recruitment process**  Participants will be recruited using advertising posters and word of mouth from the Monash University community.  **Study Procedures**  These are explained in ***Figure 2*** and in further detail below  ***Figure 2***  **Visit 1 and 2**   \| **Time (minutes)** \| **T = -30** \| **T = 0** \| **T = 2 hours** \| **T = 6 hours** \| **T = 24 hours** \| \| --- \| --- \| --- \| --- \| --- \| --- \| \| **Intervention** \| - Cannula insertion and initial blood sample \| - CRH or placebo injection - Further blood sample \| - Blood sample \| - Blood sample - Cannula removal \| - Blood sample   **END OF VISIT 1 AND 2** \|   **Visit 3 and 4**   \| **Time (minutes)** \| **T = -30** \| **T = 0** \| **T = 2 hours** \| **T = 6 hours** \| **T = 24 hours** \| \| --- \| --- \| --- \| --- \| --- \| --- \| \| **Intervention** \| - Cannula insertion and initial blood sample \| - High fat , high carbohydrate meal to participant - Further blood sample \| - Blood sample \| - Blood sample - Cannula removal \| - Blood sample   **END OF VISIT 3 AND 4** \|   *Participants will be asked to obtain from alcohol and intense exercise for 3 days prior to each of the study visits.*  **Screening visit**  Participants will be invited to meet with the study staff in order to ensure eligibility and seek informed consent. They will be informed whether or not they meet inclusion criteria at the end of the screening visit. They will be given a list of foods which are low in fat and carbohydrates. These are the only foods that they will be able to consume for the duration of the visits.  *All blood tests will involve 2x 10ml blood test tubes drown from the participants’ vein unless otherwise stated*  **Visit 1**   - Participants will, if they wish, have a light breakfast consisting of foods from a prespecified list which have a low fat and low carbohydrate content. - On presentation to the department, participants will be randomised to receive either a CRH or placebo injection. - They will then have a cannula inserted and have blood drawn. This will be the Time (T) = -30 minute blood test. - Participants will have a further blood test at the T=0 mark and then have either CRH or placebo injected into their cannula. - They will have further blood tests at the T=2 and T= 6 hour marks. - Participants will be asked to remain near the department for the duration of the study visit and will be offered a light hearted video to watch for the period of their visit. - After T=6 hours, the cannula will be removed and participants will be free to leave the department. - A low fat, low carbohydrate late lunch meal will be provided to the participants on completion of   this visit and instructions for how to prepare a low fat, low carbohydrate dinner will be given to them to follow for their evening meal.  **Visit 2**   - Participants will be asked to return the day after Visit 1 – at T = 24 hours post the initial CRH or placebo injection in order to have their final blood tests.   ***Visits 1 and 2 will be replicated during visits 3 and 4 with the alternative intervention.***  **Visit 5**   - Participants will be asked to present to Monash University, The Alfred Hospital campus. - They will have a cannula inserted and have blood taken. This will be the T = -30 sample - They will then receive the high fat meal. - ***Participants will not be informed of the nature of the meal that they are receiving*** - They will eat the meal and have the second blood test immediately after they have finished eating. This will be the T = 0 blood test. - They will have further blood tests at T = 2 and T = 6 hour mark, after which time they will have their cannula removed and they will be free to leave the department. - A low fat, low carbohydrate late lunch meal will again be provided to the participants on completion of this visit and instructions for how to prepare a low fat, low carbohydrate dinner will be given to them to follow for their evening meal.   **Visit 6**   - The participant will be asked to return at the 24 hour mark where they will have a further blood test performed.   **Outcome measures**  ***Primary outcome measures:***  Change in intestinal permeability over the different time points in response to CRH, placebo and meal challenge as measure by:   - - Serum I-FABP, Serum CD14, serum syndecan-1 and Serum LBP as measured by the ELISA   **Data Collection/Gathering**  After obtaining informed consent, data will be collected on the participants’ demographics. This will be stored in a secure, password protected database in a re-identifiable fashion. Paper records will be kept on site at Monash university in a secure location.  **Participant Safety and Withdrawal**  ***Risk management and safety***  ***The potential for intravenous CRH administration to cause side effects***  CRH is a hormone naturally produced in the human hypothalamus in response to stress. Its intravenous preparation is used routinely in clinical practice for the diagnosis of Cushings syndrome at a dose of 200 μg.^13^ CRH has rarely been associated with side effects such as flushing and tachycardia when administered at doses ***greater*** than 200 μg and its pharmacology has been thoroughly characterised in multiple previous studies.^13,16^ We are proposing to administer 100 μg, which is half of that used in routine clinical practice. Multiple studies have been performed on healthy human volunteers and higher at this dose of CRH with no reported side effects aside from *some minor facial flushing* in one study 30 minutes post administration.^13,15,19^ Participants will be monitored in the presence of medical staff throughout this period.  ***The standardised challenge meal***  The standardised meal will provide 56-60 g total fat, 82 g carbohydrate and 28-30 g protein and will consist of two sausage, egg and cheese sandwiches with two hash browns. This challenge meal has been used in similar studies.  ***Pain/discomfort/distress during interventions, particularly cannulation for CRH administration and blood taking***  Participants will all undergo informed consent where a member of the investigator team will be able to guide them through the interventions. They will be reassured and informed that they can stop being involved in the study at any point of their choosing. Cannulation, blood taking and CRH administration will be performed by an experienced medical practitioner. The cannula will remain in-situ for no longer than the duration of the visit (6.5 hours). This is well below the recommended 72 hours (or 3 days) of cannulation duration in Australian hospitals.  ***Withdrawals***  Participants are able to withdraw from the study at any point in time. The data will be collected up until the withdrawal from the study and included in the final analysis.  ***Replacements***  If a participant chooses to withdraw from the study prior to completion a further patient will be recruited until a total of 10 patients have completed the study.  **Storage of blood and data security**  ***Blood and Tissue Storage***  Two vials of serum will be stored in aliquots for further analysis. These samples will be assigned to the participant’s research code and will remain within the Monash University at the Alfred Hospital. After analysis has been completed the blood and tissue will be destroyed.  ***Data Security***  Electronic records of participant data will be kept securely with the principal investigator whilst paper records will be kept at Monash university. At the completion of the study all records will be kept with the principal investigator for at least 7 years. All electronic records will require password access and paper records will be in security tag accessible areas within locked storage units.  **Data Analysis**  Given that this is the first study investigating the timeline of intestinal permeability change in response to the described stimuli, a sample size of 10 participants has been chosen to initially explore these effects. The median values of the quantitative results of the ELISA will be compared between the 3 different conditions. Non parametric paired analyses will be performed and a statistical criterion of p<0.05 as significant will be adopted. | |

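### The label T=0 marks a pre-stimulus sample on injection days but an end-of-meal sample on the meal day, so the meal is compared with the injections on a different clock

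*Protocol*

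**What the plan says.** All places are in the protocol.

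- **Injection days** (Study Procedures, Visit 1; repeated at Visits 3 and 4 with the other injection). The first sample comes at cannulation: "They will then have a cannula inserted and have blood drawn. This will be the Time (T) = -30 minute blood test". Then: "Participants will have a further blood test at the T=0 mark and then have either CRH or placebo injected into their cannula". Visit 2 confirms that time is counted from the injection, since the last sample is due "at T = 24 hours post the initial CRH or placebo injection".
- **Meal day** (Visit 5). The first sample again comes at cannulation: "They will have a cannula inserted and have blood taken. This will be the T = -30 sample". Next, "They will then receive the high fat meal", and then "They will eat the meal and have the second blood test immediately after they have finished eating". Of that second sample the text says "This will be the T = 0 blood test". The 2 h and 6 h samples follow on the same scale, and Visit 6 adds a 24 h sample without restating what it is counted from.
- **Figure 2.** The T=0 cell of the injection table reads "CRH or placebo injection - Further blood sample". The T=0 cell of the meal table (headed Visits 3 and 4, although the text puts the meal at Visit 5) lists the meal and then a sample.
- **Use of the data.** The primary outcome is change across the time points under CRH, placebo and meal. Data Analysis compares median ELISA values between the three conditions with paired non-parametric tests. The second aim is to find the best sampling times. No baseline sample is named.

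**The concern.** The protocol uses one set of time labels for three conditions that it intends to compare, but the zero point differs. On injection days T=0 is a second pre-stimulus sample and the clock starts at the stimulus. On the meal day T=0 is the first post-stimulus sample and the clock starts when the stimulus ends.

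Two things are at stake. First, a comparison at T=0 is not like with like, and any baseline that includes T=0 removes early response from the meal condition but from neither injection condition. The Background expects I-FABP and syndecan-1 to leak quickly because they are preformed, so these two markers are the most exposed. LBP and sCD14 need new protein synthesis and are expected to lag. Second, timing is itself an aim, and a label such as 2 h does not mean the same interval from stimulus onset in each condition.

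**Working it through.** The protocol gives no figure to reproduce here: the sample size of 10 is stated as exploratory, and no effect size or variance is given. The check sets the procedures side by side and does simple clock arithmetic.

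**1. Role of each early sample, from the visit text**

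| Sample | CRH day | Placebo day | Meal day |
|---|---|---|---|
| T=-30 | pre-stimulus | pre-stimulus | pre-stimulus |
| T=0 | pre-stimulus | pre-stimulus | after the meal |
| Pre-stimulus samples | 2 | 2 | 1 |

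**2. Effect of the choice of baseline**

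Let R be the true rise of a marker at a later time on the meal day, and r the rise already present at the end of the meal. Relative to the pre-meal level, T=-30 is 0 and T=0 is r. The estimated meal change is then:

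- baseline T=-30: R − 0 = R
- baseline T=0: R − r
- baseline the mean of both: R − (0 + r)/2 = R − r/2

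On injection days both samples precede the stimulus, so no response is subtracted whichever baseline is used. The loss of r or r/2 falls on the meal condition alone. The documents give no value for r.

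**3. Offset of the clock**

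Eating time is not stated. A nominal upper limit follows from two entries: the first sample is labelled T=-30 minutes, and the section on discomfort during interventions limits cannulation to the 6.5 h visit, with the cannula removed after the 6 h sample. So 6.5 − 6 = 0.5 h is available from the first sample to T=0, and the meal lies within it.

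If d is the eating time, a meal-day sample labelled t falls t + d after the start of eating, and the relative shift is d/t. It is assumed that the 24 h meal sample is counted from T=0, as the 2 h and 6 h samples are. The value d = 0.25 h is an illustrative assumption; 0.5 h is the nominal limit.

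| Label | d = 0.25 h | d = 0.5 h |
|---|---|---|
| 2 h | 2.25 h (12.5%) | 2.5 h (25%) |
| 6 h | 6.25 h (4.2%) | 6.5 h (8.3%) |
| 24 h | 24.25 h (1.0%) | 24.5 h (2.1%) |

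On injection days the same labels are 2, 6 and 24 h after the stimulus. The offset matters at 2 h and is small from 6 h on.

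**4. Which comparisons are touched**

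CRH and placebo days follow the same order, so their contrast is unaffected. Meal versus placebo and meal versus CRH are affected, mainly at T=0 and 2 h.

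**The case against.** The strongest reply is that no harm follows from the text alone. No baseline is named, its choice is commonly left to a statistical analysis plan that is not at hand, and T=-30 is a sound common baseline already collected. Nor does Data Analysis spell out a test of T=0 against T=0. This stands: the baseline bias is conditional. It does not remove the point, because sampling order and time labels are protocol procedures. An analysis plan can name a baseline, but it cannot re-anchor the clock unless meal start times are recorded, and the protocol does not ask for them.

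Four stronger readings are tempting, and the document does not support them.

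- *A reader might infer that the meal comparisons lack a valid baseline.* They do not: the T=-30 sample precedes the meal.
- *A reader might infer that the meal-day clock is unbounded because eating time is not fixed.* The T=-30 label and the 6.5 h visit limit the gap to about 30 minutes, at least nominally.
- *A reader might infer that Figure 2 sets a third, conflicting order by listing the injection before the sample.* Two items in one cell need not be a sequence, the text is offered as the fuller account, and the meal cell agrees with Visit 5. Only the injection cell needs clearer wording.
- *A reader might infer that the second meal-day draw should move to before the meal.* That would remove the only meal sample before 2 h, and so the only one able to show early release of I-FABP and syndecan-1.

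It is also fair that a meal is not a bolus, so start or end of eating is a convention. The convention still has to be the same kind of anchor in all conditions, or be stated as different.

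**Conclusion.** The point holds, with moderate severity. As written, T=0 is a pre-stimulus value under CRH and placebo and a response value under the meal, and time is counted from the stimulus in the first two but from its end in the third. A comparison at T=0 is not interpretable as a contrast of conditions at a common time. A baseline that includes T=0 would understate the meal response by r or r/2, mainly for I-FABP and syndecan-1. Later meal samples are up to about 0.5 h further from stimulus onset, which is at most 25%, 8.3% and 2.1% of the 2, 6 and 24 h intervals.

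This rests on the Visit 1 and Visit 5 text being followed as written and on the nominal 30-minute gap being kept. The size of r is unknown. Against sampling gaps of 4 h and 18 h, a shift of half an hour is unlikely to change which of the later time points looks best. A must-fix rating would go too far: CRH versus placebo is untouched, a common baseline exists, the study is exploratory, and a clarification of labels and times resolves the matter.

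**What to change.** 1. Keep the draw at the end of the meal, but relabel it as an end-of-meal response sample. Do not compare it with the pre-injection T=0 sample.
2. Name the T=-30 cannulation sample as the baseline for all three conditions.
3. Define time zero as the start of the stimulus (injection, or start of eating) in all conditions, and count 2, 6 and 24 h from it.
4. Record the start and end time of the meal for each participant, so that actual times can be used.
5. Make the T=0 cells of Figure 2 agree with the visit text, stating whether the sample comes before or after the stimulus.

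The cost is small: edits to Visits 5 and 6 and Figure 2, two recorded times per participant, and no extra blood. The second pre-injection sample is given up as a baseline in comparisons with the meal; it can still serve in CRH versus placebo. The change should be made before sampling starts, because meal times that were not recorded cannot be recovered.

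### Withdrawn participants' data are promised for the final analysis, but the stated paired comparisons cannot use all of them, and replacements are not tied to the vacated CRH/placebo sequence

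*Protocol*

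**What the plan says.** Three parts of the protocol bear on this.

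- **Withdrawals** (under Participant Safety and Withdrawal): "The data will be collected up until the withdrawal from the study and included in the final analysis".
- **Replacements** (the next paragraph): if someone withdraws, "a further patient will be recruited until a total of 10 patients have completed the study". Nothing is said about which injection order that person receives.
- **Data Analysis**: "a sample size of 10 participants has been chosen to initially explore these effects". Then: "The median values of the quantitative results of the ELISA will be compared between the 3 different conditions". Then: "Non parametric paired analyses will be performed and a statistical criterion of p<0.05 as significant will be adopted".

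On design, the Visit 1 text says: "On presentation to the department, participants will be randomised to receive either a CRH or placebo injection". The text after Visit 2 says: "Visits 1 and 2 will be replicated during visits 3 and 4 with the alternative intervention". The Visit 5 text then gives the meal to everyone, with the last sample at visit 6. So only the CRH/placebo order is randomised, and in the visit text the meal always comes third. The tables under Figure 2 place the meal at visits 3 and 4 instead. The two accounts need to be reconciled; what follows uses the visit text.

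**The concern.** A paired test compares two or three values from the same person. Someone who left with only one condition measured has nothing to pair, so the protocol commits to including data that its stated comparison cannot take in. The target of 10 is also counted in completers, so those who leave early are replaced by people who stay.

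The second issue is sequence. In a two-period comparison with a plain paired test, equal numbers in the CRH-first and placebo-first orders are what cancel any drift between first and second session. If a replacement need not take the vacated order, a balanced start can become unbalanced. At stake are some bias in the CRH-placebo contrast if periods differ and, even with perfect balance, lost power because an unmodelled period difference adds to the spread of the paired differences.

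**Working it through.** **Inputs from the protocol:** 10 completers; three conditions; randomised CRH/placebo order; meal last (visit text); paired non-parametric tests at p<0.05. There is no stated power, effect size, SD or dropout rate, so the figure of 10 cannot be re-derived.

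**Assumptions:** 1 to 3 withdrawals, unrelated to sequence; a blocked 5:5 start; coin-flip allocation of replacements; period shift c of 0.5 or 1 SD of the paired CRH-placebo difference; normal paired differences; two-sided tests.

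**1. Who enters which comparison**

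| Leaves | CRH vs placebo | Meal contrasts | Three-condition test |
|---|---|---|---|
| Before a second condition | no | no | no |
| After both injection sessions, before visit 5 | yes | no | no |
| After some samples of the meal session | yes | at time points reached | at time points reached |

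With w withdrawals, all lost before the meal, a three-condition complete-case analysis omits w/(10+w) of entrants: 1/11 = 9.1%, 2/12 = 16.7%, 3/13 = 23.1%.

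**2. Sequence balance after replacement**

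Balance survives only if the number of replacements drawn into each sequence equals the number lost from it.

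- w=1: P(match) = 1/2, so balance is lost in 50%.
- w=2: the losses from one sequence are 0, 1, 2 with probabilities 2/9, 5/9, 2/9; the replacements into it are 0, 1, 2 with probabilities 1/4, 1/2, 1/4. P(match) = 2(2/9)(1/4) + (5/9)(1/2) = 7/18, so balance is lost in 61%. P(7:3 or worse) = 2(2/9)(1/4) = 11%.
- w=3: losses of 0 to 3 have probabilities 1/12, 5/12, 5/12, 1/12; replacements 1/8, 3/8, 3/8, 1/8. P(match) = 2(1/12)(1/8) + 2(5/12)(3/8) = 1/3, so balance is lost in 67%. P(7:3 or worse) = 2[(1/12)(4/8) + (5/12)(1/8)] = 19%.

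**3. Bias from imbalance**

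The period difference adds +c to the paired difference in one sequence and −c in the other. The unadjusted mean difference is therefore shifted by c(n1−n2)/10: 0 at 5:5, 0.2c at 6:4, 0.4c at 7:3, 0.6c at 8:2.

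**4. Type I error, unadjusted exact signed-rank test (simulated, n=10)**

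| Split | c = 0.5 SD | c = 1 SD |
|---|---|---|
| 5:5 | 0.030 | 0.007 |
| 6:4 | 0.036 | 0.015 |
| 7:3 | 0.057 | 0.058 |
| 8:2 | 0.101 | 0.191 |

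**5. Power at exactly 5:5 for a 0.8 SD effect (simulated)**

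| Analysis | c = 0 | c = 0.5 SD | c = 1 SD |
|---|---|---|---|
| Signed-rank, period ignored | 0.60 | about 0.49 | about 0.26 |
| Paired t adjusted for period | 0.60 | 0.60 | 0.60 |

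**6. Why balance still matters after adjustment**

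The adjusted estimate is the average of the two sequence means, with variance proportional to (1/n1 + 1/n2)/4. At 5:5 this is 0.100; at 7:3 it is (1/7 + 1/3)/4 = 0.119, which is 19% larger.

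**7. The meal**

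With the meal always third, the meal indicator and a period-3 indicator are the same column. A model with three conditions and three periods has five fixed-effect columns but rank 4, so a separate period-3 effect cannot be estimated.

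**The case against.** The strongest reply is that much of this rests on silence. The test, analysis sets, period term and randomisation method are often left to a statistical analysis plan, and none is shown here. That stands in part. A reader might infer that the trial ignores period or leaves sequence balance unprotected; the protocol says neither, so these are risks to close and not proven errors. The conflict between the inclusion sentence and the paired method is different, because both are written in the protocol.

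Other stronger readings also go too far:

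- **All withdrawn participants are dropped and the result is completers-only.** Not so for CRH versus placebo, where anyone with both injection sessions still forms a pair. Partial data could also enter the medians by condition or within-session changes from baseline.
- **Replacement selects people who tolerate CRH.** The protocol gives no dropout rate and reports only minor facial flushing in one earlier study. Such selection is possible but not shown.
- **The unadjusted test has inflated error.** Averaged over coin-flip allocation of all 10, its error is 0.050. It is clearly above 5% only conditionally, at 8:2 or worse.

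It is also fair to say that this is a small exploratory study and that a mixed model is one choice among several. That is why a period-adjusted rank test is offered as an equal alternative below.

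**Conclusion.** The point holds in limited form. The promise to include withdrawn participants' data cannot be kept in the between-condition comparisons for anyone who leaves before a second condition, nor in the meal contrasts for anyone who leaves before visit 5. With no withdrawals this conflict changes no number.

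The replacement rule leaves a balanced start open to drift, and the bias that follows is proportional to a period effect that the protocol does not quantify. The power loss from leaving period out does not depend on withdrawals: it occurs at 5:5 too and is large if the shift is near 1 SD. The withdrawal counts, block start, coin-flip replacement and period shifts are all assumptions. The change is worth making because it is cheap; nothing here shows that the trial's result would be wrong without it.

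**What to change.** 1. In Replacements, state that a replacement takes the CRH/placebo sequence of the participant replaced. A 5:5 start then stays 5:5.
2. Analyse CRH versus placebo with a period-adjusted method using all available data. Either fit a mixed model on log concentration with a random participant effect and terms for condition, period (injection sessions only), time, condition-by-time and the T=-30 value, or use a period-adjusted rank test. Keep the plain signed-rank test as a sensitivity analysis.
3. For the meal, fit no separate period-3 term. State that under the visit text the meal is fully confounded with period, so meal contrasts carry any drift over time. Reconcile the visit text with the Figure 2 tables.
4. Limit the inclusion sentence to what the chosen analysis can use. The mixed model can take single-session participants; the rank test needs both injection sessions.

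**Cost:** a few sentences, with no extra participants, visits or samples. The period term uses one degree of freedom, and power at 5:5 with no period effect stays at 0.60. The mixed model relies on approximate log-normality, which the signed-rank sensitivity analysis helps to check.
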